## Abstract

**Background:**

French Guiana, an overseas territory located in the Guiana Shield in South America, faces unique social and demographic challenges, particularly in relation to migration. Haitians represent 1 of the 3 largest foreign communities in the region and face specific barriers to health care access and prevention. They are also a population exposed to HIV infection.

**Objective:**

This Parcours d’Haïti study aims to update knowledge on the health of the Haitian population residing in French Guiana. From a quantitative standpoint, the primary objective of this study was to assess the frequency of sexual behaviors that expose Haitian individuals to HIV risk after arriving in French Guiana and explore the association of this risk with their living conditions. This study adopts a transdisciplinary approach to understand the broader determinants of health and the processes underlying HIV transmission.

**Methods:**

This mixed methods study involves a quantitative epidemiological and biographical analysis of Haitian individuals aged 18 to 60 years who have lived in French Guiana for more than 3 months. The biographical component uses a detailed grid that tracks key life events since birth. The qualitative component includes 3 substudies based on semistructured interviews and focus groups with Haitian people and health care professionals. These aim to deepen understanding of health care access, use of traditional and biomedical care, and mental health among Haitians. A phylogenetic component describes the distribution of clades of the Pol gene in the viruses of people living with HIV. The study materials were cocreated with local stakeholders. Recruitment of this partially hidden population used an innovative method involving all local actors and targeting key locations frequented by the Haitian community. Data collection and recruitment were carried out by Haitian Creole–speaking peer investigators (community health mediators).

**Results:**

Over 20 months between 2021 and 2023, the Parcours d’Haïti study was implemented in French Guiana. Anticipated results suggest that the main reasons for migration include insecurity and fleeing violence. Upon arrival, Haitian people likely experience significant economic hardship and social isolation. Mental health deterioration is expected, with high rates of posttraumatic stress disorder. People living with HIV are expected to face heightened vulnerability compared to HIV-negative individuals even though they already struggle with precarious living conditions. The qualitative findings regarding health care use indicate that Haitian people encounter numerous barriers to accessing health care, such as administrative complexity, language, and financial and mobility issues. The anthropological results are expected to emphasize the magical-religious origins of HIV and the use of plants and traditional medicine for its treatment. Phylogenetic results are anticipated to show a high prevalence of Caribbean B HIV subtypes.

**Conclusions:**

The Parcours d’Haïti study aims to provide valuable insights into the health determinants and HIV-related risks in the Haitian population in French Guiana. These findings should help refine health care policies and practices to better meet the specific needs of this population.
Trial Registration: ClinicalTrials.gov NCT05174234; https://clinicaltrials.gov/study/NCT05174234

**International Registered Report Identifier (IRRID):**

DERR1-10.2196/63586

## Introduction

French Guiana is a French South American overseas territory in the Guiana Shield close to the Amazon with a population of 286,618 inhabitants in 2021 [1]. Because of its location and history, this territory is inhabited by people of diverse origins and nationalities [2]. As a result, more than 60 languages are spoken in French Guiana, and approximately one-third of today’s population was born abroad [1-3]. Migration from Haiti represents a major social and demographic challenge in French Guiana [2]. According to 2017 census data, 9.3% of the population in French Guiana originated from Haiti, 1 of the 3 main foreign communities along with those from Brazil and Suriname. It is estimated that 1 in 10 inhabitants speaks Haitian Creole in daily life [3]. Population movements from Haiti have existed since the country’s political turbulence in the 80s and were reinforced by the earthquake in 2010, the closure of the Dominican border in 2015, the 2018 social crisis in Haiti, and the assassination of the Haitian president in 2021. Studies conducted on the sexual health of migrant women in French Guiana in 2021 showed that Haitian women make up the vast majority of the cohorts in health centers set up to welcome migrants, suggesting that migration flows from Haiti continue to be very dynamic [4].

French Guiana is a territory where precariousness is common, with more than half of Guianese inhabitants having a low standard of living and more than 20% having a very low standard of living [5]. This reality particularly affects households where the reference person was born abroad—in that case, more than three-quarters live below the poverty line [5]. After arriving in French Guiana, people’s living conditions deteriorate, not only in terms of housing but also socially and administratively—many people arriving and living in French Guiana do not have a residence permit [4].

French Guiana also faces major health challenges. In 2020, life expectancy at birth was still lower than in continental France in a context of dynamic birth rates [6,7]. In total, 7 major health determinants have been identified by the Haut Conseil de la Santé Publique (High Council for Public Health), including sexual and reproductive health, gender equality, infectious risks, food, nutrition, and mental health [8].

French Guiana is the French territory most affected by HIV, with a prevalence >1% in the general population [9]. Most people living with HIV in French Guiana are of foreign origin [10]. Recent studies in French Guiana (one based on the slope of CD4 decline and the other on virus phylogeny) showed that, among the foreign population living with HIV, more than half had been infected in French Guiana [10,11]. The link between migration and living conditions in the country of arrival has already been established. The Agence Nationale de Recherches sur le Sida et les hépatites virales (the French National Agency for Research on AIDS and Viral Hepatitis; ANRS) Parcours 2012 to 2013 study highlighted the issue of HIV acquisition in the Île-de-France region and late detection of chronic hepatitis B virus (HBV) infections among immigrants from sub-Saharan Africa in relation to their poor living conditions after arriving in France [12,13].

In terms of health and history, Haiti is a country that has been particularly affected by HIV since the 1970s and throughout the epidemic [14]. In 2021, according to the World Bank, 1.8% of the Haitian population was living with HIV [15]. The Haitian population in French Guiana is disproportionately affected by HIV infection—according to surveillance data, 46% of the HIV cohort participants under follow-up in the Cayenne Hospital outpatient department originated from Haiti. Between 2013 and 2018, Haitians represented 36.4% of new HIV infections in French Guiana [16]. Diagnoses are often made later than for native-born people—for Haitian people living with HIV, the time between seroconversion and diagnosis was 4.5 years on average (compared with 3.1 years for people living with HIV born in France) and was 5 years higher among men than among women [17]. The magical-religious importance and impact of stigma has already been explored among the Haitian population in French Guiana [18]. Some diseases, notably HIV, have a high level of social stigma, which can have an impact on people’s use of prevention and care. A similar observation can be made for hepatitis B. In French Guiana, the prevalence of chronic HBV infection is estimated at nearly 1.5%, compared with 0.3% in continental France. Once again, Haitians are particularly affected— the presence of the hepatitis B surface antigen (a marker of hepatitis B infection) concerns 2.5% of Haitian women registered in the French Guiana pregnancy registry [19].

Another study on knowledge, attitudes, and practices showed the high frequency of risky sexual behavior that can expose people to HIV among migrants without, however, specifying them by country of origin. Notably, 35.6% of participants reported engaging in risky behaviors over the previous 12 months (including inconsistent condom use with casual or commercial partners, having multiple sexual partners, or engaging in concurrent partnerships) [20]. A phylogenetic study conducted in French Guiana showed that people from Haiti were less likely to have viruses from large transmission clusters than other immigrants and were more likely to have viruses from small transmission clusters or dyads [11]. Thus, we hypothesize that there are particular conditions leading to a singular epidemiology in this community.

In addition to these local data focusing on sexual health and infectious diseases, international literature highlights several health issues among Haitian migrants worldwide that should be investigated in French Guiana [21,22]. Research suggests that their access to cervical cancer prevention and screening may be inadequate. The mental health of those who have experienced adversity may be impaired, these experiences, along with cultural differences between caregivers and patients, may influence the modalities of care [23,24]. In addition, common health issues could have consequences linked to poorer access to care [25]. The interrelationships among traditional medicine, vodou, herbal medicine, and modern medicine need to be explored [26].

Therefore, all these factors seem to point to the particular needs regarding health, sexual and reproductive health, and rights of the Haitian population, a large and growing part of French Guiana’s population. The Haitian population in French Guiana is a key population for public health in terms of improving not only their health but also the health of the entire Guianese population.

We hereby describe the Parcours d’Haïti study protocol, conceived to update knowledge on the Haitian population living in French Guiana using a transdisciplinary approach to gain a detailed understanding of health determinants and underlying processes of HIV or HBV infection.

## Methods

### Study Objectives

From a quantitative perspective, using notably a biographical approach, the main objective of this study was to evaluate the frequency of sexual behavior exposing people from Haiti to the risk of HIV infection after their arrival in French Guiana and its association with their living conditions. Secondary objectives consisted in describing migration routes, living conditions, access to health insurance coverage and health care, contacts with medico-social structures, social support, general state of health, mental health, and levels of food insecurity after arrival in French Guiana. With regard to sexual and reproductive health and rights, the objectives were to study the delay in first screening for sexually transmitted infections (STIs), as well as the factors associated with earlier screening; study the delay in entry into care and retention in care for people living with HIV or HBV and their determinants; and investigate the use of birth control methods, the frequency of wanted and unwanted pregnancies, and the use of abortion. With regard to emotional life, the objectives were to describe the relational and sexual life.

From a qualitative exploratory perspective, the objectives were to investigate and describe the social representations of HIV and HBV infections and their impact on the use of prevention and biomedical and traditional care. In addition, representations of the Guianese health care system and its prevention services were explored, as well as an anthropological understanding of representations of the body and illness in relation to the ethnomedicinal conceptions of people of Haitian origin living in French Guiana. Finally, another objective was to explore the obstacles to and facilitators of accessing mental health care and understand the mental health problems encountered and the responses provided to migrants in French Guiana from the point of view of health professionals, social workers, and local nongovernmental organizations (NGOs). From a phylogenetic perspective, we aimed to describe the distribution of clades of the Pol gene in the viruses of people living with HIV from Haiti.

Hence, the Parcours d’Haïti study is a mixed methodology study. First, a quantitative component based on an epidemiological (cross-sectional and biographical) study was conducted using a questionnaire and a hetero-administered biographical grid. The questionnaires were administered by Haitian Creole–speaking mediators, for the most part from the local community. Mediators were recruited for their linguistic expertise and interpersonal skills and then trained to collect complex data effectively. Second, a qualitative component based on a socioanthropological ancillary study using participant observation and semistructured interviews (itself developed along several dimensions) was conducted. Third, a phylogenetic analysis of HIV Pol gene sequences based on sequences collected as part of routine care (a resistance genotype analysis is systematically performed before antiretroviral therapy initiation) was conducted. The qualitative component of the research was conducted primarily by a Haitian Creole–speaking anthropologist with extensive experience in studying Creole societies supported by 2 researchers trained in qualitative methodologies.

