### Study Populations and Inclusion Criteria

For the quantitative epidemiological and biographical component, participants were included in 3 groups: a general population group, a group of people living with HIV, and a group of people living with HBV.

The inclusion criteria for all groups were as follows: being born in Haiti (regardless of current nationality), having been in French Guiana for >3 months, being aged between 18 and 60 years, and having no objection to participate in the study. For the group of people living with HIV, the inclusion criteria were as follows: living with HIV and having a diagnosis dating back >3 months (whatever their status with regard to hepatitis B and C), as well as being followed up on by one of the study’s partner physicians at the hospitals in Cayenne, Kourou, or Saint-Laurent-du-Maroni; in outpatient care; or by a partner association. For the group of people living with chronic hepatitis B, the inclusion criteria were living with a chronic HBV infection and having been diagnosed for >3 months (not coinfected with HIV), as well as being followed up on by one of the study’s partner physicians in the hospitals of Cayenne, Kourou, or Saint-Laurent-du-Maroni; in outpatient care; or by a partner NGO.

For the general Haitian population group (not known to live with HIV or HBV), the inclusion criteria were declaring that they were not infected with either HIV or HBV, being under the care of one of the study’s partner physicians, or being recruited in the public space of one of the cities targeted by the study (Cayenne, Matoury, Rémire-Montjoly, Macouria, Kourou, Montsinéry-Tonnegrande, Sinnamary, Maripasoula, Saint-Laurent-du-Maroni, or Mana). Exclusion criteria were being unable to answer the interviewer in French or Haitian Creole; being under guardianship, tutelage, or legal protection; and having already answered the study questionnaire.

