#### Statistical Analysis of Quantitative and Biographical Data

With regard to the statistical analysis of quantitative information, the major indicators will be described using percentages as well as means or medians with their SDs or IQRs depending on their distribution. Analytical work will be carried out with a biographical and social epidemiology approach using the tools of epidemiological analysis to study the associations between behaviors and health indicators and social determinants. Factors associated with biographical key indicators will be analyzed year after year using discrete-time logistic regression models that take into account time and the values of indicators collected in the biographical grid year after year [31]. Factors associated with indicators collected at the time of the study will be analyzed using Poisson regression with robust variance. The Stata software (StataCorp) will be used to conduct the analyses.

An analysis of the participants’ support and care structures will be carried out based on specific questions that will be analyzed through clustering and a bipartite network approach using methods derived from graph theory. These analyses will provide a better understanding of the levers and care itineraries that can be developed. The R software will be used for these analyses (*tidyverse* and *tidygraph* packages).

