During these years, people may be exposed to situations of sexual vulnerability and to unwanted sexuality and transactional, paid, or even forced sex, exposing them to a greater risk of acquisition of HIV or STIs and psychological trauma. In terms of sexual health, we hypothesize that, regardless of the participant group, a large proportion of the population has been exposed to sexual violence and transactional relationships and that these phenomena particularly concern women. Finally, we hypothesize that the use of contraception is low and that recourse to abortion is very limited.

Concerning the follow-up of people living with HIV and people living with HBV, we hypothesize that Haitian populations in French Guiana use screening relatively early and that those diagnosed with HIV enter care relatively early, in line with the screening and mediation services available in the region, notably through the French Red Cross. We also think that impaired social conditions, social isolation, and low health literacy are associated with a delay in screening. A catch-up certainly exists for women during pregnancy. It is likely that periods of disruption of care are closely linked to the social situation of the people concerned, which changes from year to year. The biographical approach will enable us to confirm the hypothesis that, in the years during which a disruption in care occurred, the person faced social or administrative difficulties more often. In addition, we assume that periods of loss to follow-up are more frequent among people living with HBV, linked to an incomplete understanding of the disease, the absence of therapeutic indications for a large proportion of people living with HBV, prolonged follow-up intervals, and a lower civil society investment than that in people living with HIV. With regard to people living with HIV, we hypothesize that they will report unprotected sex in the years following their infection.

Finally, we hypothesize that conducting a long interview focusing on health issues is likely to contribute to respondents’ access to and use of health care.

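### Entry into care and retention are to be studied in HIV and HBV groups admitted only if already followed up, so entry delays are right-truncated and current or permanent loss is not observable

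*Protocol article*

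**What the plan says.** Under Study Objectives, one secondary aim is to "study the delay in entry into care and retention in care for people living with HIV or HBV and their determinants". A separate clause of the same sentence is to "study the delay in first screening for sexually transmitted infections (STIs), as well as the factors associated with earlier screening"; it is not limited to any group.

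Under Study Populations and Inclusion Criteria, the HIV group requires "living with HIV and having a diagnosis dating back >3 months", "as well as being followed up on by one of the study’s partner physicians at the hospitals in Cayenne, Kourou, or Saint-Laurent-du-Maroni", with outpatient care or a partner association as alternatives. The HBV group requires "living with a chronic HBV infection and having been diagnosed for >3 months (not coinfected with HIV") and the same kind of follow-up, with a partner NGO as the alternative. The general group must declare that it has neither infection.

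The analysis section states that "Factors associated with biographical key indicators will be analyzed year after year using discrete-time logistic regression models". The article mentions no truncation adjustment and no weighting.

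Under Assumptions and Hypothetical Study Outcomes, the authors expect that "those diagnosed with HIV enter care relatively early", and write that "we assume that periods of loss to follow-up are more frequent among people living with HBV".

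Patients lost to follow-up appear in two places. Sample Size cites them as a reason why the active hospital files understate the pool available. Limitations cites them as a reason why the recruitment targets were ambitious. The selection bias named under Limitations concerns the choice of recruitment sites.

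**The concern.** Being in follow-up is both an entry condition and the outcome. A diagnosed person still waiting to enter care cannot join the HIV or HBV group. Nor can someone who entered care and is now lost, unless a partner association or NGO still follows them. If they know and state their status, they cannot join the general group either.

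Three things are at stake:

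- **Entry delay.** Nearly every sampled delay has already ended, so long delays are under-represented. This favours the hypothesis of early entry.
- **Determinants of delay.** Truncation removes more people from the slower-entering subgroup, so the contrast between subgroups shrinks.
- **HBV versus HIV loss to follow-up.** Currently lost people are missing from both groups in unknown and possibly unequal proportions, so the comparison is not identified. Expected Follow-up nonetheless plans to use the results to help prevent loss to follow-up.

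**Working it through.** **1. The plan's own figure.** The only design calculation is for a proportion: n = z²π(1−π)/Δ² = 1.96² × 0.25 / 0.05² = 384.16. This reproduces the stated 384 per group, raised to 400. It does not bear on delay or retention. The article gives no delay distribution and no number lost, so what follows is illustration.

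**2. Who can contribute data.**

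| Diagnosed person | Can join the HIV/HBV group? | What the data show |
|---|---|---|
| Entered care, followed up now | Yes | Completed delay; past interruptions |
| Left care, then returned | Yes | Completed delay; the interruption |
| Never entered care | Largely no | Nothing |
| Left care, not returned | Largely no | Nothing |

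A discrete-time logistic model handles people still waiting as censored person-years. Here they contribute no person-years at all, so the model has nothing to correct with.

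**3. Entry delay.** Assumptions: exponential delay D with true median m, rate λ = ln 2 / m; time since diagnosis T uniform on 0.25 to 10 years; sampled only if D ≤ T.

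- Share sampled: P(D ≤ T) = 1 − (e^(−0.25λ) − e^(−10λ)) / (9.75λ). For m = 1, λ = 0.693 and the share is 1 − (0.841 − 0.001)/6.758 = 0.88.
- The observed median x solves E[F(min(x, T))] / E[F(T)] = 0.5, with F(x) = 1 − e^(−λx).

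| True median (years) | Observed median (years) |
|---|---|
| 0.25 | 0.24 |
| 0.5 | 0.47 |
| 1 | 0.85 |
| 2.1 | 1.45 |
| 3.5 | 1.87 |

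The window matters. For true medians of 0.5, 1, 2 and 4 years, a 5-year window gives 0.43, 0.71, 0.99 and 1.20; a 20-year window gives 0.48, 0.93, 1.70 and 2.81.

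**4. Determinants.** Take two subgroups with true medians of 2 and 4 years, so the true hazard ratio (slow to fast) is 2/4 = 0.50. In the 10-year window their observed mean delays are 1.89 and 2.49 years. The crude ratio of entries per person-year is then 1.89/2.49 = 0.76, so a barrier that halves the entry rate looks about half as strong.

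**5. Retention.** Assume 15% of people in care drop out each year, 30% of those out return each year, and time since entry is 1 to 15 years. Among people in care at the end, yearly dropout appears as 10.6% instead of 15%, and the share ever interrupted as 50% instead of about 66%. Conditioning on being in care now therefore thins out past interruptions too.

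**6. Restricting to older diagnoses.** With diagnoses at least 5 years old in the same 10-year window, a true median of 3.5 years appears as 2.43 rather than 1.87. The bias is reduced, not removed.

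**7. Feasibility text.** The HBV target is 400 against 250 in active hospital follow-up. If hospital files were the only source, (400 − 250)/400 = 37.5% would have to come from outside them. Sample Size points to lost patients for this margin, but the inclusion criteria do not admit people who are not followed up.

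**The case against.** The case for the plan has real strength in four places.

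- **First screening.** A reader might infer that delay to first screening is biased in the same way. The documents do not support this. That objective is not confined to the HIV and HBV groups, and the 1600 planned general participants can include never-screened people, who are censored normally. Pooling would distort: if 30% of the general group were never screened and all 800 others count as screened, the pooled figure is 0.30 × 1600 / 2400 = 20%. The article does not say it will pool the groups.
- **Retention.** A reader might also infer that all loss to follow-up is hidden. It is not. Data Collection Tools says follow-up and treatment histories were collected biographically, so interruptions followed by return are seen. The hypothesis linking years of disrupted care to social or administrative difficulties remains testable among people who returned. Follow-up by an association or NGO may also reach people with weak clinical contact, and this is why the exclusion is described as large rather than total.
- **Size.** If entry really is fast, truncation barely matters (0.25 years seen as 0.24). This stands. But observed short delays alone cannot establish fast entry, because slower entry under truncation also shortens them.
- **Place in the plan.** These are secondary objectives, and risk-set detail often sits in an analysis plan that is not shown. That lowers the severity. It does not remove the conflict, which lies between the stated objective and the stated eligibility rules.

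**Conclusion.** The point holds for delay from diagnosis to care and for retention in the HIV and HBV groups. Eligibility conditions on the outcome, the stated model does not repair this, and the stated limitations do not name it. The direction for entry delay is towards shorter delays, in line with the early-entry hypothesis. The size cannot be fixed from the documents: under the assumptions above it runs from negligible (true median 0.25 or 0.5 years) to nearly half (3.5 seen as 1.87). The retention figures rest equally on assumed dropout and return rates.

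Overall retention and the HBV-versus-HIV difference in loss to follow-up cannot be estimated from this sample. Past interruptions among people now followed up can be described, as a conditional quantity. This should be fixed, but it does not threaten the study: the primary objective and its sample size are untouched.

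**What to change.** The article says analyses had not begun at submission, so the following can be written into the analysis plan and the report:

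1. State the target population for the care objectives as people currently followed up.
2. Analyse diagnosis-to-care delay with a right-truncation method, for example reverse-time hazards, and report it as conditional on having entered care. Use restriction to older diagnoses only as a sensitivity analysis.
3. Define the retention outcome as past interruptions among people now in care. Dropping the interview year from the risk set would not remove the conditioning. Make no claim about overall retention or about HBV-versus-HIV loss to follow-up.
4. For delay to first screening, give the general group as the main estimate, or weight the groups if they are combined.
5. Name this selection under Limitations, separately from the choice of sites.
6. Reconcile Sample Size, which counts lost patients towards feasibility, with the inclusion criteria.

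The cost is some extra analysis and narrower conclusions. No new data are needed.
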